### **10.2.2. Secondary efficacy endpoints**

For the assessment of secondary efficacy endpoints, specific models will be used for continuous outcomes (e.g., changes in physical performance, nutritional status, functional status, cognitive function, and quality of life). Specifically, changes over time between groups will be assessed by a repeated-measure mixed model with terms for intervention, time, baseline score, baseline score by intervention interaction, and time by intervention interaction. For outcomes such as incidence of falls and mortality rate, the analysis defined for the primary efficacy outcome will be replicated (except for the secondary analysis with competitive risk for the mortality rate). Additional analyses (e.g., subgroup composite endpoint analyses) will be defined in agreement with the Managing Board and the Data Safety Monitoring Board and specified in the statistical analysis plan that will be produced prior to the beginning of the analyses.

Please note that within this section, we have limited the description of the analysis plan to the major SPRINTT hypotheses. Nevertheless, the relevance and amount of the data collected during the project will certainly lead to ancillary and secondary analyses always within the scopes and objectives of SPRINTT. Such secondary plans will be developed after formal approval and validation by the Managing Board of SPRINTT.

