### **Derivation of primary endpoint**

Disability will be considered ascertained:

- at the date of the 400-meter walk test, if participants fail to walk 400 meters within 15 minutes, or need an assistive device
- or at the date of the visit (or date of the 400-meter walk test if available) when the visit is performed but the participant did not perform the 400-meter walk test and the adjudication (automatic or from the committee) does not classified the event as no disability (i.e. ascertained or not conclusive) if any

- or at the date of death if the participants died during the study

Participants who have not met this disability criterion at the end of their study participation (including withdrawals) will be considered as right-censored observations. The censoring time will be calculated as the date of their last successful completed 400-meter walk test (including assessment of “no disability” by the automatic adjudication or the adjudication committee) minus the date of randomization visit V1-T0 (or date of randomization if V1 is missing) + 1 day.

**Particular cases:** In the case where more than 9 months are observed between two consecutive visits or between the last available visit and the death:

- If the disability criterion is not met at the 2nd consecutive visit, then participants will be censored at the date of their first consecutive visit. In the case where the first of the two consecutive visits is the randomization visit, then the censoring time will be equal to 1.
- If the disability criterion is observed at the 2nd visit of the two consecutive visits, or the participant died more than 9 month after the last available visit, then the disability will be considered ascertained at the date of the first consecutive visit or at the date of the last available visit before to die, plus 183 days (i.e., 6 months). In the case where the first of the two consecutive visits (or the last available visit before to die) is the randomization visit, then the disability will be considered ascertained at the date of randomization visit V1-T0 (or date of randomization if V1 is missing) + 183 days.

If no post-baseline visit is done, then participants will be censored at the date of randomization visit V1-T0 (or date of randomization if V1 is missing).

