### **2.1.3.2 Secondary efficacy endpoint(s)**

The timing of all secondary endpoints assessments are specified in the study flowchart (in Appendix A).

The secondary efficacy endpoints include:

- Changes in physical performance measures from baseline to Month 24 and Month 36, assessed by:
  - The total SPPB score computed directly in the corresponding e-CRF page (ranging from 0: low performance to 12: high performance)
  - The usual gait speed in m/s, assessed by the ratio of the 4 meters walks divided by time (faster of the two walks of the gait speed test)(see details in [Section 2.5.2](#))
  - The handgrip strength (maximum reading in kg)

- Changes in disability status from baseline to Month 24 and Month 36, assessed by:
  - The Lawton IADL score (ranging from 0 to 8; the higher the score, the greater the participant's abilities) obtained from the Pepper Assessment Tool for Disability (PAT-D) questionnaire computed directly in the corresponding e-CRF page
  - The KATZ ADL score obtained from the PAT-D questionnaire (ranging from 0 [participant totally dependent] to 6 [participant independent])
- Time (in days) from the randomization to the date of first occurrence of persistent mobility disability, operationalized as the failure to complete the 400-metre walk test within 15 minutes or as the assessment of disability by the adjudication in two consecutive visits, or as a first mobility disability followed by the death:
  - Persistent mobility disability will be considered ascertained:
    - at the date of the first test failure among the 2 consecutive available test failures, whatever the time interval between the 2 consecutive visits, if the first test failure is observed no more than 9 months after the previous test success
    - Or at the date of the last available test failure before the date of death, whatever the time interval between the failure and the death, if the test failure is observed no more than 9 months after the previous test success
    - Or at the date of the success test (including baseline test) + 183 days (i.e. months 6) if a persistent disability (i.e. 2 consecutive observed failure tests whatever the time interval between the 2 consecutive visits, or one failure test followed by the death) is observed more than 9 months after the previous test success
  - Participants will be censored:

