    - at the date of last available test (failure or success) or date of death if no persistent mobility disability observed and no more than 9 months between two consecutive visits or between the last available successful test and the death,
    - or at the date of the first test (failure or success) where the following test is observed more than 9 months after the previous test, and no persistent disability is observed.

Notes: The baseline assessment is considered as a successful test in this endpoint definition.

If no post-baseline visit is done, then participants will be censored at the date of randomization visit V1-T0 (or date of randomization if V1 is missing).

- Changes in body composition measures from baseline to Month 24 and Month 36, assessed using DXA (centralized reading):

- $aLM^{BMI}$ , in males and females
  - $aLM$  in kg, in males and females
- Changes in anthropometric parameters from baseline to Month 24 and Month 36, assessed by:
  - Weight in kg, assessed using percent change
  - Body mass index (BMI) in  $kg/m^2$ ,
  - Calf circumference in cm,
  - Waist circumference in cm,
  - Hip circumference in cm,
  - Mid-arm circumference in cm
- Changes in nutritional status from baseline to Month 24 and Month 36 assessed by the Mini Nutritional Assessment-Short Form (MNA-SF) score computed directly in the corresponding e-CRF page (ranging from 0 to 14: a score of 12 or greater indicating satisfactory nutritional status and a score strictly below 8 indicating malnutrition)
- Changes in cognitive function from baseline to Month 24 and Month 36, assessed by the Mini Mental State Examination (MMSE) score computed directly in the corresponding e-CRF page (ranging from 0 to 30: a score of 27 or greater indicating normal cognitive function, between 19 and 24 indicating mild cognitive impairment, between 10 and 18 indicating moderate cognitive impairment and a score of 9 or below indicating severe cognitive impairment)
- Changes in Cumulative Illness Rating Scale (CIRS) from baseline to Month 24 and Month 36, computed directly in the corresponding e-CRF page:
  - Total score (ranging from 0 to 56)
  - Severity index (ranging from 0 to 4)
  - Comorbidity index (ranging from 0 to 14)
- Changes in mood from baseline to Month 24 and Month 36 using the Center for Epidemiological Studies-Depression scale (CES-D):

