### **Supportive analysis**

A supportive analysis will be performed by excluding deaths from the definition of the disability event (described in [Section 2.1.3.1](#)). Participants who have not met the disability criterion before to die will be considered as right-censored observations. The censoring time will be calculated as the date of their last successful completed 400-meter walk test minus the date of randomization visit V1-T0 (or date of randomization if V1 is missing) + 1 day.

Same methodology as described above in [Section 2.4.4.1](#) for the primary efficacy endpoint will be used to analyze the time (in days) from randomization visit V1-T0 (or date of randomization if V1 is missing) to the date of first occurrence of major mobility disability using the new disability definition that excludes deaths.

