Time to first occurrence of persistent mobility disability will be compared, as for the primary analysis endpoint, in the randomized population with a baseline SPPB score <8 within the intervention arm, using a two-sided Log-rank's test stratified by study site and gender. Hazard ratio (and 95% CI) between intervention groups will be estimated using a Cox proportional hazard model with the stratification factors of study site and gender as covariates.

The cumulative incidence functions for the 2 intervention arms will be summarized using Kaplan-Meier method and displayed graphically. The cumulative incidence rate over

time at each scheduled time-points of the protocol together with appropriate 95% confidence interval will be provided.

The time to complete the TMT-A test and the TMT-B test, as well as, the 7-day average of total steps, sitting and lying activity (hours), standing activity (hours) and stepping activity (hours) from ActivPal accelerometry will be summarized by visit using number, median, Q1, Q3, minimum and maximum. In addition, results overtime will be presented graphically using boxplots.

For other efficacy parameters not normally distributed, a non-parametric approach will be used. Descriptive statistics will be summarized using median, Q1, Q3, minimum and maximum.

All secondary endpoints analyses will be provided also in the randomized population with a baseline SPPB  $\geq 8$  assigned by randomization.

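### Disability risks in the supportive analysis and for persistent mobility disability are read from Kaplan-Meier curves that censor deaths without the event, so they are overstated in both arms

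*Combined protocol and SAP*

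**What the plan says.** **Persistent mobility disability.** SAP section 2.1.3.2 counts two consecutive failures as the event, "or as a first mobility disability followed by the death". Otherwise, where no gap exceeds 9 months, the participant is censored "at the date of last available test (failure or success) or date of death if no persistent mobility disability observed". Section 2.4.4.2 then says: "The cumulative incidence functions for the 2 intervention arms will be summarized using Kaplan-Meier method and displayed graphically". It adds a rate with a 95% confidence interval at each scheduled visit.

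**Supportive analysis.** The supportive part of SAP section 2.4.4.1 removes death from the disability event: "Participants who have not met the disability criterion before to die will be considered as right-censored observations". Their censoring time is the last successful walk test, not the date of death. The method is carried over ("Same methodology as described above in" section 2.4.4.1), and that section contains the same Kaplan-Meier sentence.

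**Primary endpoint, for contrast.** Disability is also ascertained "or at the date of death if the participants died during the study" (SAP section 2.1.3.1), so death is part of the event.

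**Protocol.** Section 10.2.2 says the primary analysis will be replicated for outcomes such as falls and mortality, "except for the secondary analysis with competitive risk for the mortality rate". Neither protocol section 10.2.1 nor the SAP defines a competing-risk analysis.

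**The concern.** Someone who dies without the event can no longer have it. Censoring keeps that person's share of risk in play, as if the event were still to come. One minus Kaplan-Meier then describes risk in a population where nobody dies first, and even that only if death and disability are independent. It is not the proportion who become disabled, which is what cumulative incidence means. The direction is fixed: too high in each arm as soon as one such death precedes a later event.

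At stake are the absolute risks and intervals planned for each visit, in frail people aged 70 and over. The supportive analysis will be read closely because it is nearest to the protocol's own primary outcome, which is failure of the 400-m walk with no death component.

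**Working it through.** **1. The design figure.** The documents state no cumulative incidence, so the related figure to reproduce is the event count in protocol section 10.1 (hazard ratio 0.75, two-sided 5%, 85% power, 1:1):

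events = 4(1.960 + 1.036)² / (ln 0.75)² = 434. This agrees with the plan.

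**2. Disability hazards implied by the design.** Inputs from protocol section 10.1 are 1,200 participants with SPPB below 8 (600 per arm), 12-month accrual, 3-year maximum and 25% exponential dropout over two years. The dropout hazard is g = −ln(0.75)/2 = 0.144 per year. With uniform accrual, the expected events per arm are

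600 × average over follow-up u from 2 to 3 years of λ/(λ+g) × [1 − exp(−(λ+g)u)].

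Setting the total to 434 with hazard ratio 0.75 gives λ = 0.254 per year (HALE, about 241 events) and 0.191 per year (MCI, about 193 events). All 434 are treated as disability events, as in the protocol's endpoint. The SAP's event also includes death.

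**3. The two quantities at 36 months**, with μ the hazard of death before disability:

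- Kaplan-Meier target: 1 − exp(−3λ)
- Cumulative incidence: λ/(λ+μ) × [1 − exp(−3(λ+μ))]

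The documents give no μ, so 1% to 8% per year is assumed.

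**4. Supportive analysis** (percent; excess taken before rounding). Kaplan-Meier gives 53.39 for HALE and 43.59 for MCI in every row, a difference of 9.80.

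| Deaths per year | HALE incidence | HALE excess | MCI incidence | MCI excess | Arm difference |
|---|---|---|---|---|---|
| 1% | 52.70 | 0.69 | 43.00 | 0.59 | 9.69 |
| 3% | 51.35 | 2.04 | 41.86 | 1.73 | 9.48 |
| 5% | 50.05 | 3.34 | 40.77 | 2.82 | 9.28 |
| 8% | 48.19 | 5.20 | 39.19 | 4.39 | 8.99 |

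The relative excess runs from about 1% to 11%.

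**5. Persistent disability**, assuming half the hazards in step 2. Kaplan-Meier gives 31.7% (HALE) and 24.9% (MCI).

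- At 3% deaths per year, the incidence is 30.4% and 23.9%: excess 1.3 and 1.0 points.
- At 5%, it is 29.6% and 23.2%: excess 2.1 and 1.7 points.

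**6. Check by simulation.** This used 40,000 participants per arm, the visit schedule and the main censoring and event rules, the full hazards from step 2, pre-disability death at 1% to 5% per year, and three times that rate after disability (assumed). Kaplan-Meier was compared with Aalen-Johansen.

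- Supportive endpoint: excess 1.0 to 4.3 points (HALE) and 0.8 to 3.5 points (MCI).
- Persistent disability, with a failure followed by death counted as an event: 0.7 to 3.2 and 0.6 to 2.5 points. The upper ends exceed step 5 because the hazards are not halved.
- Censoring deaths at the last successful test or at the date of death gave practically the same Kaplan-Meier value (52.62% both ways for HALE at 3%). The excess therefore comes from the estimator, not from the censoring date.

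**The case against.** The case against acting is that little depends on these curves. The primary endpoint already counts death. Mortality has its own log-rank test, Cox model and curves (SAP section 2.4.5.3). Secondary endpoints are exploratory (section 2.4.4.3), and the other analysis is only supportive. A log-rank test or Cox model with death censored is a valid cause-specific comparison. The arm difference moves from 9.8 to 9.5 points at 3% deaths per year. All of this stands and limits the weight of the point. It does not make the reported percentages correct.

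Some stronger readings are tempting, and the documents do not support them:

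- A reader might infer that every death is censored for persistent disability. Section 2.1.3.2 makes a failure followed by death an event, so only deaths with no earlier failed test are censored.
- A reader might infer more bias in the arm with more deaths. The excess also depends on the disability hazard. At 3% per year in both arms, death-first risk, μ/(λ+μ) × [1 − exp(−3(λ+μ))], is 6.6% in MCI and 6.1% in HALE, yet MCI has the smaller excess (1.7 against 2.0 points).
- A reader might infer that the SAP dropped a promised analysis. The protocol's phrase is a parenthesis about mortality that refers to nothing defined. It commits the plan to no method for these two endpoints.
- A reader might infer that the bias feeds the health-economic model. That work is in a separate document (SAP section 2.1.6), and the effectiveness measures that the protocol gives as examples do not include these curves.

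**Conclusion.** The point holds for two sets of outputs: the absolute risks in the supportive analysis and those for persistent mobility disability. As written, the SAP will report values that are too high in both arms. The direction needs no assumption beyond some deaths without the event preceding later events.

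The size is conditional. With design-implied hazards and 1% to 8% deaths per year, the 36-month excess in the supportive analysis is about 0.7 to 5.2 points (HALE) and 0.6 to 4.4 points (MCI). For persistent disability it is about 1 to 2 points at half those hazards and 3% to 5% deaths per year. The death rates, constant hazards, the halving, and counting all 434 events as disability are assumptions.

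No primary or confirmatory conclusion changes. This is a low-severity correction that is worth making.

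**What to change.** For these two endpoints, in SAP sections 2.4.4.1 (supportive analysis) and 2.4.4.2:

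- Estimate cumulative incidence with the Aalen-Johansen estimator and its 95% confidence interval, with death without the event as a competing event.
- Date the competing event at the recorded date of death, not the last successful walk test. Changing the estimator alone would not be enough in the supportive analysis, because deaths there are coded as censored at that test.
- For deaths long after the last visit, apply the existing 9-month gap rule. Under section 2.1.3.1, a death more than 9 months after the last visit is dated 183 days after that visit.
- In section 2.1.3.2, state when censoring is at the last test and when it is at death. The present wording offers both.
- Keep the stratified log-rank tests and the Cox models as planned, and describe them as cause-specific.

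No new data are needed, since death is already recorded for the mortality analysis (section 2.1.4.3). The cost is one extra event-date derivation, a few lines of SAP text, and slightly lower reported percentages.

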#### **2.4.4.3 Multiplicity issues**

In order to handle the multiple comparisons of the primary endpoint in the randomized population with a baseline SPPB score  $< 8$  and then in the whole randomized population, the type-I error will be controlled by the use of the sequential inferential approach. Only if the primary analysis in the randomized population with a baseline SPPB score  $< 8$  is statistically significant ( $p < 0.05$ ), the comparison of the primary endpoint between arms will be extended to the whole randomized population. The tests for the primary endpoint will be performed two-sided at level alpha equal to 0.05.

The secondary efficacy endpoints will be analyzed for exploratory purpose only.

#### **2.4.5 Analyses of safety data**

The summary of safety results will be presented by intervention arm in the randomized population with a baseline SPPB score  $< 8$  assigned by randomization, and in the randomized population with a baseline SPPB score  $\geq 8$  assigned by randomization separately.

The “observation period” defined in [Section 2.1.4](#) is applicable to all safety analyses for the classification of AEs, determination of abnormality/potential abnormality values and the last on-study value for the laboratory and vital signs.

#### **General common rules**

All safety analyses will be performed on the randomized population, using the following common rules:

- All the data from the randomization visit V1-T0 (or date of randomization if V1 is missing) will be considered in safety analyses

- For each safety parameter, the baseline for each participant is defined as the screening visit value or the randomization visit (V1-T0) value, whichever is the latest one.
- Abnormality/potential abnormality values are defined as values considered medically important according to predefined criteria/thresholds defined in the protocol for clinical laboratory test and vital signs [Appendix B and Appendix C])
- Abnormality criteria will determine which participants had at least one post-baseline abnormality during the emergent adverse event period, taking into account all evaluations performed during the study, including nonscheduled or repeated evaluations. The number of all such participants will be the numerator for the post-baseline abnormality percentage
- The post-baseline abnormality denominator by intervention arm for a given parameter will be based on the number of participants who have that parameter assessed during post-baseline assessments.
- All measurements, scheduled or withdrawal visit (V9), will be assigned to analysis windows defined in [Section 2.5.4](#) in order to provide an assessment for Month 3 to Month 36 time points.
- For quantitative safety parameters based on laboratory or vital signs measurements, descriptive statistics will be used to summarize results and change from baseline values by visit and intervention arm using analysis windows as defined in section 2.5.4.
- Summaries will include the last on-study value. The last on-study defined as the last available value collected at or just prior to the study end.

#### **2.4.5.1 Analyses of adverse events**

##### ***Generalities***

The primary focus of adverse event reporting will be on the emergent adverse events.

If an adverse event date is incomplete, an imputation algorithm will be used to classify the adverse event as pre-emergent, emergent or post-emergent. The algorithm for imputing date will be conservative and will classify an adverse event as emergent unless there is definitive information to determine it is pre- or post-emergent. Details on classification of adverse events with missing or partial onset dates are provided in Section 2.5.3.

Adverse event incidence tables will present by SOC, HLGT, HLT, and PT, sorted by the internationally agreed order for SOCs and in alphabetic order for HLGT, HLT and PT within a SOC in alphabetical order for each intervention arm, the number (n) and percentage (%) of participants experiencing an adverse event and the number and rate of AEs per patient-year. The denominator for computation of percentages is the randomized

population with a baseline SPPB score  $<8$ , and the randomized population with a baseline SPPB  $\geq 8$  respectively, within each intervention arm.

Sorting within tables ensures the same presentation for the set of all AEs within the observation period (pre-emergent, emergent, post-emergent). For that purpose, the table of all emergent adverse events presented by SOC and PT sorted by the internationally agreed SOC order and decreasing frequency of PTs within SOC will define the presentation order for all other tables unless otherwise specified. In case of equal frequency regarding PTs, alphabetical order will be used.

